### Exclusion criteria

4.3

1.Drugs for PMDD were used within 3 months.2.History of drug abuse.3.Those who participated in clinical trials of other drugs within the previous month.4.Serious hepatic disease, heart disease, kidney disease, blood system disease or malignant disease.5.Currently pregnant or breast-feeding.6.Ovariectomy, abortion or contraceptive use within 6 months.

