## Introduction

1

Premenstrual syndrome (PMS) refers to the periodic physical, mental and behavioral changes of women in the luteal phase.^[1]^ Premenstrual dysphoric disorder (PMDD) is a serious form of PMS.^[2]^ Mental symptoms are the main characteristics of PMDD, such as depression, anxiety, irritability, and so on, appearing in the late luteal phase and ending shortly after menstruation.^[3]^ The incidence of PMDD varies from 3% to 8% for premenopausal women.^[4]^ Cyclically recurring premenstrual symptoms seriously affect women's health and daily life,^[5]^ are even related to suicidal ideation.^[6]^ The pathogenesis of PMDD is still insufficiently clear, studies indicate that many factors can cause PMDD, such as hormonal changes, neurotransmitters, diet, stress, and so on.^[7,8]^ The comorbidities of PMDD with other mental disorders are high, a retrospective study showed that more than 50% of women with PMDD had diagnosis of major depression disorder.^[9]^ The therapeutic goal of PMDD is to relieve premenstrual emotional and physical symptoms.^[10]^ In most cases, pharmacotherapy of antidepressants is the main therapy, such as selective serotonin reuptake inhibitors (SSRIs) and other serotonergic antidepressants.^[11]^ The antidepressant medications have positive antidepressant-like effects, but a range of side effects cannot be ignored, such as fatigue, nausea, decreased libido, sweating, and so on.^[11]^

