### Diagnostic criteria

4.1

The Clinical diagnostic criteria of PMDD is based on the 5th edition of the *Manual of Diagnosis and Statistics of Mental Diseases* (DSM-5).^[2]^ The TCM syndrome of liver-qi depression in the study follows the *Guidelines for Clinical Research of new*

*Chinese Medicine*.^[26]^ In addition, PMS severity criteria should also be met, including the follows:

1.A postmenstrual phase (days 6–10) daily average ≤2.5 for each symptom.2.A premenstrual phase (day −5 to −1 before menstruation) daily average ≥3.0 for 3 distinct items.3.A premenstrual phase daily average worsened by at least 50% compared with the corresponding postmenstrual phase daily average for 3 distinct items.4.A score ≥3 on functional impairment items for at least 1 day during the premenstrual phase.

The diagnostic standards of TCM syndrome of liver-qi depression are as follows:

1.Primary symptoms and signs include premenstrual depression and (or) irritability, breast pain, chest tightness, and ability reduction of work, family management, learning and communicate.2.Secondary symptoms and signs include chest and hypochondriac distention pain, sighing frequently, lower abdomen falling distention, anorexia, fatigue, menstrual abdomen pain, menstrual blood suspending fluid retention, retarded menstruation.3.In addition, the patient has a pale or dark tongue, fat body of tongue, thin white or yellow coated tongue, and a stringy thin or stringy slow pulse.

Patients who meet the following criteria can be diagnosed as PMDD liver-qi depression syndrome: 3 primary and secondary symptoms/signs, combined with the tongue and pulse conditions, symptoms appearing before menstruation and disappearing after menstruation for 2 menstrual cycles or more continuously.

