### Inclusion criteria

4.2

Participants of PMDD with liver-qi depression syndrome will be included:

1.Clinical diagnostic criteria of PMDD according to the DSM-5.2.Women aged between 18 and 30 years.3.Regular menstrual cycle of 21 to 35 days (fluctuation range <3d).4.Clear mind and independent judgement.5.Able to sign informed consent and cooperate voluntarily.

Participants of healthy people will be included:

1.Female college students and graduate students, aged between 18 and 30 years.2.Regular menstrual cycle (21–35 days).3.Clear mind and independent judgement.4.Able to sign informed consent and cooperate voluntarily.5.Physical health (Consistent with World Health Organization definition of Health).

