### Intervention

4.4

Sixty participants will be assigned to Xiaoyaosan treatment group and normal control group respectively with a ratio of 1:1. Participants in Xiaoyaosan treatment group will be required to take Chinese patent medicine with Xiaoyaosan (Xiaoyao Pills, 8 pills) orally with warm water 3 times a day for 3 menstruation cycles continuously. The medicine will be taken from the luteal phase and stopped during the menstrual period of each menstruation. The Xiaoyaosan will be manufactured as pills and provided by Jiuzhitang Co., Ltd. Participants in normal control group will not be intervened. Any other treatments for PMDD will not be allowed during the study. If the condition deteriorates, participants can withdraw from the study and choose modern drug therapy, such as SSRI antidepressants. Study visits will take place at baseline and at 1, 2, 3 menstrual cycle.

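### The six exclusions in Section 4.3 do not cover current suicidality, although the Introduction links premenstrual symptoms to suicidal ideation and Section 4.4 allows no other PMDD treatment for three cycles

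*Protocol article*

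**What the plan says.** The Introduction describes the hazard. It states that recurring premenstrual symptoms "are even related to suicidal ideation", and it adds that "a retrospective study showed that more than 50% of women with PMDD had diagnosis of major depression disorder".

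Section 4.3 gives six numbered exclusions: recent PMDD medication, drug abuse, recent participation in another drug trial, serious disease, pregnancy or breast-feeding, and recent ovariectomy, abortion or contraceptive use. The serious-disease item is "Serious hepatic disease, heart disease, kidney disease, blood system disease or malignant disease". The medication item is "Drugs for PMDD were used within 3 months".

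Section 4.2 has five inclusion items for the PMDD group. The one closest to mental state is "Clear mind and independent judgement". Section 4.1 adds severity limits, among them a postmenstrual (days 6 to 10) "daily average ≤2.5 for each symptom".

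On treatment during the study, Section 4.4 says "Any other treatments for PMDD will not be allowed during the study". It gives one way to other medication: "If the condition deteriorates, participants can withdraw from the study and choose modern drug therapy, such as SSRI antidepressants". Section 6 lets any participant leave at any time, and Section 7 has all adverse events recorded and graded.

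**The concern.** The plan names suicidal ideation as something associated with the condition under study, and it limits what else the enrolled women may take. One would expect the entry rules to keep out a woman who is actively suicidal when she is assessed, and they do not. The women with PMDD all receive a product whose effectiveness is the question of the trial. Recruitment runs partly through internet advertisements and posters (Section 3.2), so an earlier clinical assessment cannot be assumed for every volunteer.

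What is at stake is the safety of an individual woman: someone who needs prompt psychiatric care could be enrolled and asked to forgo other PMDD treatment for three cycles. No estimate, test or sample size depends on the point.

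**Working it through.** The plan has no figure to reproduce. The check is a reading of the entry and exit rules against one case: a woman with DSM-5 PMDD who has active suicidal thoughts in the premenstrual phase at the time of entry.

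**Step 1: does any exclusion in Section 4.3 apply to her?**

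| Item in 4.3 | Covers suicidality? |
|---|---|
| 1. PMDD drugs in the last 3 months | No |
| 2. Drug abuse | No |
| 3. Another drug trial in the last month | No |
| 4. Serious disease (five groups, all somatic) | No |
| 5. Pregnancy or breast-feeding | No |
| 6. Ovariectomy, abortion or contraceptives in the last 6 months | No |

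Result: 0 of 6.

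**Step 2: does an inclusion or diagnostic rule keep her out?** None of the five PMDD inclusion items in Section 4.2 refers to suicidality. The item "Clear mind and independent judgement" concerns capacity to decide, and a woman can have capacity and still have suicidal thoughts. The postmenstrual limit in Section 4.1 tends to remove women whose symptoms persist through the cycle. It does not remove a woman whose thoughts are confined to the premenstrual phase, and that is the pattern to which the Introduction's remark refers.

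**Step 3: what happens once she is in?** Other PMDD treatment is not allowed. With three cycles (Section 3.1) of 21 to 35 days (Section 4.2), the treated period is 3 × 21 = 63 to 3 × 35 = 105 days.

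**Step 4: does the exit in Section 4.4 reach her?** It is conditional on the condition getting worse. Thoughts that were present at entry and have not changed do not plainly meet that condition. The general right to withdraw in Section 6 is open to her, but it relies on her own initiative.

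**Step 5: cost of a baseline question.** The time per woman is an assumption of 3 to 5 minutes, because the document gives none.

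- Asked of the 30 women with PMDD: 30 × 3 = 90 min (1.5 h) to 30 × 5 = 150 min (2.5 h).
- Asked of all 60 participants: 60 × 3 = 180 min (3 h) to 60 × 5 = 300 min (5 h).

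Women who are screened and not enrolled would add to this. Their number is not stated.

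**The case against.** The strongest reply is that the plan already has safeguards. Entry needs a DSM-5 diagnosis, severity limits and symptoms that clear after menstruation over at least two cycles, so persistent depression tends to be screened out. Women are seen at baseline and at each of the three cycles, may leave at any time and are followed up if they do. Adverse events of any kind are recorded, and researchers may stop observation. The rule on earlier medication selects women who are already off PMDD drugs and takes nothing away from them. All of this stands, and it is why the point is minor. None of it keeps out a woman who is actively suicidal at entry.

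A second reply is that a journal article condenses a fuller protocol. That has force for visit procedures but less for exclusions, since Section 4.3 presents them as a numbered list.

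Two stronger readings are tempting and are not supported:

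- A reader might infer that the trial never asks about suicidal thoughts during follow-up. This cannot be judged. Table 1, the schedule of assessments, is not shown, and the wording of the DRSP items is not given.
- A reader might infer from the figure of more than 50% that about half of the treated women would have major depression. The figure comes from a retrospective study and is not described as current depression in women who meet the limits of Section 4.1.

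It is also fair to say that premenstrual ideation may go with more severe PMDD, so an exclusion may shift a 30-woman group towards milder cases. This is a real cost, and it argues for a narrow threshold.

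**Conclusion.** The point holds for eligibility. As printed, Sections 4.2 and 4.3 admit a woman with active suicidal thoughts at entry, and the exit in Section 4.4 is worded too narrowly to cover her clearly. The severity is minor: it is a safety improvement to a small non-randomised pilot that already has free withdrawal and adverse event recording, and it has no bearing on the efficacy analysis.

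The conclusion assumes that the list in Section 4.3 is complete as printed. The number of women affected is left open because the document gives no rate of suicidal ideation. Nothing is concluded about enquiry at later visits.

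**What to change.** 1. **Section 4.3:** add a seventh exclusion for current active suicidal ideation (with plan or intent) or a recent suicide attempt. The sponsor's clinicians should write the time window for a recent attempt into the text. The wording should count the latest premenstrual phase as current, because a woman seen after menstruation may be free of such thoughts that day.
2. **Baseline visit:** the investigator checks the criterion with a direct question and refers any woman who answers positively.
3. **Section 4.4:** extend the exit so that suicidal thoughts at any time are a ground for leaving the study and receiving other treatment, whether or not the condition has worsened.

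The cost is a short amendment and about 1.5 to 5 hours of staff time at existing baseline visits under the stated assumption, plus time for screened women who do not enrol. No extra visit is needed. The downside is that a few women, possibly with more severe PMDD, will be screened out. Limiting the exclusion to plan, intent or a recent attempt keeps that loss small, and the report should state how many were excluded on this ground.

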### Intervention

4.4

Sixty participants will be assigned to Xiaoyaosan treatment group and normal control group respectively with a ratio of 1:1. Participants in Xiaoyaosan treatment group will be required to take Chinese patent medicine with Xiaoyaosan (Xiaoyao Pills, 8 pills) orally with warm water 3 times a day for 3 menstruation cycles continuously. The medicine will be taken from the luteal phase and stopped during the menstrual period of each menstruation. The Xiaoyaosan will be manufactured as pills and provided by Jiuzhitang Co., Ltd. Participants in normal control group will not be intervened. Any other treatments for PMDD will not be allowed during the study. If the condition deteriorates, participants can withdraw from the study and choose modern drug therapy, such as SSRI antidepressants. Study visits will take place at baseline and at 1, 2, 3 menstrual cycle.

## Outcome measure

5

### Primary outcome

5.1

The primary outcome measure is the 21 symptom items of the Daily Record of Severity of Problems (DRSP).^[27]^ The symptoms of 60 participants will be evaluated at baseline and at 1, 2, 3 menstrual cycle by the DRSP. The average of the late luteal (premenstrual) phase for symptom items will be summed to generate the total score. The primary efficacy variable is the changes in symptom score between baseline and after 3 menstrual cycles of Xiaoyaosan treatment. In addition, the symptom score of Xiaoyaosan treatment group will also be compared with the normal control group.

### Secondary outcome

5.2

The secondary outcome is the improvement of TCM syndrome in TCM symptom score scale. The PMDD syndrome scores of TCM will be recorded by the same researcher before and after 3 menstrual cycles treatment to assess whether the treatment improved the patient's signs of PMDD. The evaluation of TCM syndrome improvement will be measured by the reduction (reduction = (before treatment score − after treatment score) / before treatment score × 100%).^[28]^

### Exploratory outcome

5.3

The exploratory outcomes will be expected to find metabonomics and small molecular marker compounds closely related to the pathogenesis of PMDD. At the same time, combined with the clinical efficacy assessment, the mechanism of Xiaoyaosan in the treatment of PMDD was further explored from the metabolic level, so as to provide a scientific basis for the rational application of this medicine. Urine of the participants will be collected at baseline and at 3 menstrual cycle. Urine will be stored at −20°C until assayed. Non-targeted metabonomics detection of urine will be used to explore the mechanism of PMDD and Xiaoyaosan by liquid chromatograph-mass spectrometer (LC-MS) technology.

## Data collection and management

6

The data will be collected from record of DRSP and TCM symptom score scale recorded by participants. The scores will be statistically managed by medical officers of the trial team. Data entry and management is the responsibility of the designated data administrator who will establish the symptom database and verification procedures. Two professionally trained operators will enter and confirm the data. After carrying out data logical proofreading, identified errors will be corrected. These data forms will be processed, signed, and dated by the investigator. The database will be locked after the database is established. If any data revision is needed after locking, a research-related signature must be provided.

The Participants are all on the premise of voluntariness in the whole process of the trial. They are allowed to withdraw at any time during the trial. All withdrawn cases will be followed up obtain information about their condition. The data will be analyzed according to the intention-to-treat (ITT) principle.

## Safety assessment

7

All safety-related variables including vital signs physical examinations, vital signs (temperature, blood pressure, breathing, and heart rate) and laboratory tests (blood count, urine and stool tests, kidney and liver function tests, and electrocardiographic examination) before and after treatment will be recorded. If adverse events (AEs)occur, it will be evaluated by using the National Cancer Institute (Bethesda, MD) Common Terminology Criteria for Adverse Events V.4.03.^[29]^ All AEs will be recorded in the Case Report Forms (CRF). The correlation between adverse reactions and drugs will be evaluated. The researchers decide whether to stop the observation or not according to the situation, and follow-up investigation should be carried out for the cases that are discontinued the observation due to adverse reactions.

## Sample size calculation

8

This study is a pilot study, so a formal sample size calculation is not completely required.^[30]^ A sample size of 60 participants will be recruited, 30 PMDD participants and 30 healthy participants. Results from this study will be applied to the sample size calculations in future studies.

## Statistical analysis

9

The data will be analyzed by using Statistical Packages of Social Sciences software (SPSS 24.0). Categorical variables will be described statistically by percentages or frequencies. Chi-square test will be used for comparison between groups. Continuous variables will be described as mean, standard deviation, median, and range. The independent *t* test or Wilcoxon rank-sum test will be used to compare continuous variables. All results presented in this study are based on two-sided tests. The value of *P* < .05 will be considered statistically significant.

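### The primary efficacy variable is a before/after change in the same treated women, but the only tests named for continuous data are for two independent samples, so no named test fits it

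*Protocol article*

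**What the plan says.** Section 5.1 (Primary outcome) of the protocol article fixes the primary variable: "The primary efficacy variable is the changes in symptom score between baseline and after 3 menstrual cycles of Xiaoyaosan treatment". Only the PMDD group receives Xiaoyaosan (Section 4.4), so this is a change within the treated women. The comparison with healthy women follows as an addition: "In addition, the symptom score of Xiaoyaosan treatment group will also be compared with the normal control group".

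Section 5.2 (Secondary outcome) has the same structure. The TCM score is "recorded by the same researcher before and after 3 menstrual cycles treatment", and improvement is expressed as each woman's percentage reduction.

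Section 9 (Statistical analysis) gives the rule for continuous data: the independent t "test or Wilcoxon rank-sum test will be used to compare continuous variables". It adds that "All results presented in this study are based on two-sided tests" and that P "< .05 will be considered statistically significant". The article mentions no paired t test, signed-rank test, one-sample test of a change or repeated-measures model.

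On size, Section 8 says "A sample size of 60 participants will be recruited, 30 PMDD participants and 30 healthy participants" and "This study is a pilot study, so a formal sample size calculation is not completely required". No SD, effect size, power or within-woman correlation is given.

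**The concern.** The independent t test and the rank-sum test both assume that the two sets of values come from different people. Baseline and cycle-3 DRSP scores come from the same 30 women. Treating them as 60 unrelated values leaves the within-woman correlation out of the standard error, so the P value set against the .05 threshold is not what it claims to be.

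At stake is mainly sensitivity. If a woman's two scores are positively correlated, as repeated symptom scores usually are, a moderate real change can be declared non-significant. There is also a cost to the pilot's stated purpose. Section 8 intends the results to feed later sample size calculations, and a later trial that analyses change would need the SD of within-woman change, which an unpaired test does not use.

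**Working it through.** **Step 1: set the sections side by side.**

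| Comparison | Where | Data structure | Does a test in Section 9 fit? |
|---|---|---|---|
| DRSP change, baseline to after cycle 3, treated women (primary) | 5.1 | same women twice | no |
| DRSP score, treated versus healthy (additional) | 5.1 | different women | yes |
| TCM score before and after treatment | 5.2 | same women twice | no |

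**Step 2: inputs.** From the document: n = 30 treated women, two-sided alpha 0.05. Assumed, because the document is silent: equal SDs at both times, bivariate normal scores, complete pairs, a within-woman correlation ρ of 0.1 to 0.7, and a true fall of 0.5 or 0.8 SD. The plan states no figure that could be reproduced first.

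**Step 3: standard error of the mean change.**
- Unpaired: SD × √(2/n) = SD × √(2/30) = 0.258 SD, whatever ρ is.
- Correct: SD × √(2(1−ρ)/n) = 0.245, 0.216, 0.183 and 0.141 SD at ρ = 0.1, 0.3, 0.5 and 0.7.

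The unpaired standard error is too large by a factor 1/√(1−ρ). It is right only at ρ = 0.

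**Step 4: true type I error of the independent t test.** The large-sample formula is 2 × [1 − Φ(1.96/√(1−ρ))]. At ρ = 0.5 this is 2 × [1 − Φ(2.77)] = 0.0056. Simulation at n = 30 gives 0.0066 to 0.0069. The rank-sum test behaves in the same way (0.021, 0.006 and 0.0008 at ρ = 0.3, 0.5 and 0.7).

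**Step 5: power.** The independent test is simulated. The paired test uses the noncentral t distribution with 29 degrees of freedom and noncentrality (δ/SD) × √n / √(2(1−ρ)). At δ = 0.5 SD and ρ = 0.5, the noncentrality is 0.5 × 5.477 / 1 = 2.74 and the power is 0.754.

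| ρ (assumed) | True type I error, independent t | Power at 0.5 SD: independent / paired | Power at 0.8 SD: independent / paired |
|---|---|---|---|
| 0.1 | 3.9% | 48% / 51% | 87% / 88% |
| 0.3 | 2.0% | 47% / 61% | 90% / 95% |
| 0.5 | 0.7% | 47% / 75% | 93% / 99% |
| 0.7 | about 0.07% | 47% / 93% | 97% / >99% |

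With a paired test the type I error is about 5% at every ρ. Only a negative correlation turns the error the other way: at ρ = −0.2 the independent t test rejects a true null in 7.3% of trials.

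**The case against.** The strongest reply is that Section 9 never says the independent test will be run on baseline against cycle-3 scores. The sentence before it concerns between-group comparisons. Section 5.1 does plan such a comparison, and the named tests suit it. On this reading the article lists its between-group tests, and a fuller protocol or analysis plan supplies the within-group one. This stands to the extent that unpaired use is not proven. It does not remove the point. The continuous-data sentence carries no such limit, so the article is not silent: it states a general rule that misfits its own primary variable. If the rule is confined to PMDD versus healthy women, it tests something other than that variable.

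It can also be said that the trial is a pilot without a power target and that positive correlation makes the error conservative. Both are true and limit the harm, but the .05 threshold is still applied.

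Four stronger readings are tempting and are not supported:
- **That false claims of efficacy become more likely.** This would need a negative within-woman correlation. With a positive one, P is too large.
- **That the primary confidence interval would be wrong.** The article plans none. An interval built by the same unpaired method would be 1.17/1.38/1.79 times the paired width at ρ = 0.3/0.5/0.7, but that is hypothetical.
- **That the metabolite comparisons share the error.** Section 5.3 names no test for them and Section 9 does not mention them. For the TCM score, too, the gap is a missing test: the percentage reduction is already a within-woman quantity, and unpaired use is not shown.
- **That healthy women have almost no score to lose.** This is plausible, but Section 4.2 sets no DRSP ceiling for controls, and the Discussion says that about 95% of women of reproductive age have premenstrual symptoms.

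**Conclusion.** The point holds as a mismatch between Sections 5.1 and 9, and the text is wrong as written. Its size depends on a correlation and an effect that the document does not give. The loss matters for a moderate effect with substantial correlation: at 0.5 SD and ρ = 0.5, about 53% of real effects would be missed instead of about 25%. It is minor at ρ = 0.1 (48% against 51% power) and modest at 0.8 SD (at most about 6 percentage points in the range shown). A paired test would calibrate the P value. It would not turn an uncontrolled before/after change into evidence that the treatment caused it.

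**What to change.** In Section 9, state three things:
1. The baseline-to-cycle-3 DRSP change in the treated group is tested with a paired t test, or with the Wilcoxon signed-rank test if the changes are clearly non-normal.
2. The before/after TCM score is analysed with the same within-woman approach.
3. The independent t test and the rank-sum test are used only to compare PMDD with healthy women.

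A mixed model over baseline and cycles 1 to 3 is an option, but it is not needed to resolve the mismatch. The cost is one or two sentences. The tests are available in SPSS, and no new data, visits or participants are required. The change should be recorded before the data are analysed.
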